Correspondingly, from the feeding angle, we will bioinformatically process genomic and biochemical information available in the food space to identify and source key whole foods and food components from NZ’s food chains. We will leverage our domestic food composition and food-health databases (17) and select whole foods and food components that support the growth of the selected beneficial infant GI bacteria that are “generally accepted as safe” (GRAS). Although being an experimental diet applied in an exploratory study, the design of the ECF will ensure that both whole foods and food components will be acceptable to both the consuming babies and the purchasing parents.

STUDY OBJECTIVES

Primary objectives of the clinical pilot feasibility study are:

1. To determine whether infants will consume the target food(s) in a dose estimated to alter immune function via modification of the microbiome and associated metabolite changes.
2. To determine the feasibility of the outcome measurements (immune, microbiome, hot/microbe metabolome), assess recruitment potential, and identify high prevalence adverse events.
3. To determine the number of infants that would be required for an RCT of a complementary feeding intervention for improved immune protection from infection.
4. Which outcome variable(s) are both relevant and feasibly to demonstrate the chain of effects of whole food(s) or food component(s) on immune health benefits?

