This feasibility study will determine the power for a subsequent RCT there no sample size calculations are required. The proposed sample size of 30 infants who will receive the feeding intervention and 10 infants will receive the active control (probiotic) for a period of 6 months. This sample target is based on an achievable recruitment rate of participants within a 12 month time frame and allows for follow up for 6 months.

In addition to classical case/control analyses, every infant will not only be sampled but also analysed before and after the prebiotic feeding, i.e. being assessed as a case/control pair, in addition to classical data analysis. This “personal” case/control pairwise analysis will account for differences in infant feeding before the actual intervention (e.g. duration of breast feeding, infant formula differences) and can be interpreted as a multiplexed n-of-1 trial.

The feasibility aspect of this study will assess compliance and rate of loss to follow up. This data will be used to inform a subsequent RCT. In previous studies and prevalence studies that we have conducted in 12 to 24 month old children the recruitment rate has been approximately 2 participants per week.

Statistical methods

A multiplexed n-of-1 clinical design trial design in which every infant is sampled before and after the intervention, and followed up. Thereby constituting its own case-control pair.

Data Management

Each participant will be assigned a trial identity code which will be allocated at enrolment to allow for link-anonymisation of data. The documents and database will also use infant date of birth. All personal data will be stored on an encrypted drive with links to personal information only being available to the study co-ordination team. Paper forms and hard copies will be stored in locked filing cabinets in secure sites. Data will be consolidated by each site using the REDCap (Research Electronic Data Capture) software (RW.ERROR - Unable to find reference:1572). This is a secure web application which is password protected and not accessible by third parties. REDCap will be managed at the University of Auckland. The investigator will also keep a screening log with details of all participants screened for the trial with their name, date of birth, NHI number, and trial number. The investigators will permit monitoring, audits, review, and regulatory inspections, providing direct access to source data/documents (where appropriate).

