3. Milestone 2: Best method(s) to collect data on adherence to consuming the candidate foods (number attempted, number completed, quality).
4. To determine the feasibility of the outcome measurements (infection, immune, microbiome, host/microbe metabolome), assess recruitment potential, and identify high prevalence adverse events.
5. Milestone 1: Feasibility of measuring protection against infection using daily parental report of infection (number attempted, number completed, quality).
6. Milestone 2: Feasibility of measuring immune response to the rotavirus and pneumococcal vaccines in venepuncture blood and saliva as measures of immune function (% of children who followed the immunisation schedule, % of parents who agree to blood test, % successful blood draws in young children, data fit to purpose).
7. Milestone 3: Feasibility of using medical records as a measure of immune response
   (% of parents who agree to data access, completeness of data access, data fit to purpose).
8. Milestone 4: Feasibility and logistics of collecting 4 faecal samples between 6 and 12 months of age (number collected).
9. Milestone 5: Recruitment rate per month and extent and type of advertising required.
10. Milestone 6: Prevalence and nature of parent-reported adverse events, and identification of gross changes in growth rate.
11. To determine an appropriate sample size for the proposed full clinical trial.
    1. Milestone 1: Sample size required for the primary objective of the proposed clinical trial – improved immune protection from infection as a result of consuming the candidate food(s).
    2. Milestone 2: Sample size required for the secondary objective of the proposed clinical trial – altered microbiota as a result of consuming the candidate food(s).

Research Plan (2019 – 2024)

The present proposal aims at delivering the scientific insight and development concept to enable design and execution of a follow-up full clinical trial, informed by the pilot trial described in the present submission. The full-scale clinical study will test whether and how immune protection benefits can be conferred to infants around the weaning period by “targeted prebiotic feeding”. In contrast to the pilot trial (conducted at the Liggins Clinical Research Unit) this full trial is envisaged to be set up and performed at the “Starship Children's Health” Hospital, Auckland.

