The full CT is conceived to have three arms: (i) one group of infants will receive a prebiotic feed as informed by our ECF developments (Tranche I); (ii) the second group will receive a control complementary feeding (“standard weaning food”) as recommended and accepted in today’s infant nutrition practice; (iii) the third (smaller) group of infants will be given a probiotic control, known to show relevant immune-protection benefit(s) and accepted as infant nutrition ingredient, as a positive control (like in in the pilot trial.)

We plan to extend the omics-based molecular phenotyping from microbiomics, metabonomics, BCR sequencing, and immune cell biology, to proteomics and beyond. This comprehensive molecular phenotype will be correlated with classical clinical readouts. As tested in the pilot CT, we will analyse the full CT data by both classical group comparisons and longitudinally, with every child being analysed individually, before and after the prebiotic complementary feeding. This latter analysis is expected to deliver microbial, immune and health trajectories across the weaning period.

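### The pilot is said to determine the RCT's power and sample size, but it has no standard-food arm and cannot alone supply the control rate or the target effect

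*Protocol*

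**What the plan says.** The Sample Size section of the protocol states: "This feasibility study will determine the power for a subsequent RCT". It gives this as the reason for making no calculation of its own. Objective 3 under Study Objectives, listed among the primary objectives, is "To determine the number of infants that would be required for an RCT of a complementary feeding intervention for improved immune protection from infection". Item 11 of Clinical Pilot Study Objectives and Milestones repeats the aim and attaches two milestones. The first is "Sample size required for the primary objective of the proposed clinical trial", meaning protection from infection. The second is "Sample size required for the secondary objective of the proposed clinical trial", meaning altered microbiota. Both are framed as results of eating the candidate food.

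The Sample Size section gives the arms as "30 infants who will receive the feeding intervention and 10 infants will receive the active control (probiotic) for a period of 6 months". Trial Design calls the study non-randomised with an active control. Study Intervention describes the 10 probiotic infants as a positive control, there to show that the methods can detect a benefit. Research Approach speaks of two prebiotic diets plus a probiotic control. No description includes an arm on standard food.

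Research Plan (2019 – 2024) describes the RCT. One arm gets the prebiotic feed, "the second group will receive a control complementary feeding" of the standard weaning kind, and a third, smaller arm gets a probiotic.

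**The concern.** Sizing a two-group comparison needs a target difference, the outcome level in the control group, and nuisance parameters such as the SD, the overdispersion of illness counts, and dropout. The RCT's main control is standard weaning food. The pilot observes nobody on it, so two of these inputs cannot come from pilot data. Yet the protocol says that the pilot will determine the power, and gives this as the reason why no calculation is needed now.

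The pilot will produce two effect-like numbers: the difference between the prebiotic and probiotic groups, and the change within infants from before to after feeding. Neither estimates prebiotic food against standard food. At the end of the study these would nevertheless be the numbers to hand for meeting a primary objective and two milestones. An RCT sized on either could be much too small or much too large.

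**Working it through.** **The plan's own figure.** 30 + 10 = 40, and the five groups of 8 in Figure 1 also give 5 × 8 = 40. The protocol states no alpha, power, effect size or RCT sample size, so there is no power calculation to reproduce.

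**Which RCT inputs the pilot can supply**

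| Input | Available from the pilot? |
| --- | --- |
| Infection rate on standard food | No, there is no such arm |
| Prebiotic versus standard-food effect | No, for the same reason |
| Prebiotic versus probiotic difference | Yes, but non-randomised and against an active product |
| Before/after change | Yes, but with no concurrent untreated group |
| SD or overdispersion, completeness, adherence, dropout | Yes, with sampling error |

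The first two rows do not depend on the number of infants. The before/after change runs from about 6 to 12 months of age. It combines the food with maturation, weaning and time since vaccination (rotavirus and pneumococcal doses are scheduled up to 5 months), and nothing in the design separates these.

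**Precision of 30 versus 10, in SD units**

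- SE = √(1/30 + 1/10) = √0.1333 = 0.365.
- 95% half-width = t(0.975; 38 df) × SE = 2.024 × 0.365 = 0.74.
- Difference detectable with 80% power at two-sided 0.05 = (1.960 + 0.842) × 0.365 = 1.02.

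**If that estimate were used as the RCT effect.** Assume a true effect of 0.3 SD, two-sided alpha 0.05 and 80% power.

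- RCT size needed per arm = 2 × (1.960 + 0.842)² / 0.3² = 174.4, so 175.
- Range containing 95% of pilot estimates = 0.3 ± 1.96 × 0.365 = −0.42 to 1.02.
- P(estimate ≤ 0) = Φ(−0.3/0.365) = Φ(−0.82) = 21%.
- P(estimate > 0.6) = 1 − Φ((0.6 − 0.3)/0.365) = 21%. An estimate twice the truth gives a quarter of the required size.
- In a simulation of 200,000 draws, the resulting RCT size was below half the need in 37% of draws and within 25% of the need in 9%.
- With an assumed true effect of 0.5 SD (63 per arm needed), the chances of an estimate at or below zero, of under half the need, and of landing within 25% are 8%, 28% and 14%.

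**Nuisance parameters.** The 95% limits for the true variance, as multiples of the estimate, are df/χ²(0.975) to df/χ²(0.025). Required N is proportional to the variance.

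- 30 prebiotic infants (29 df): 0.63 to 1.81.
- Both groups pooled (38 df): 0.67 to 1.66.
- If half of 30 infants had an infection (assumed), the exact 95% interval would be 31% to 69%.

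The variance ranges are wide but usable, provided that the uncertainty is carried forward.

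**The case against.** The strongest reply is that the protocol nowhere says the RCT effect will be taken from the 30-versus-10 contrast or from the before/after change. The probiotic infants have another stated job, as a positive control. The pilot data that the Sample Size section names as informing the RCT are compliance and loss to follow-up, which are feasibility parameters. A pre-set important difference with an external control rate is compatible with everything written, and the method may be in an SAP that is not shown. The RCT will also have its own protocol and review.

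Most of this stands. A reader might infer that the RCT size derived from this pilot would be wrong. The documents do not support that, because it requires a use of the estimates that they do not state. The percentages above describe that use, and only for a continuous outcome in SD units. Infection may be analysed as a count or a proportion.

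A reader might also infer from Objective 4 that RCT outcomes will be picked for a large change in these same infants, which would inflate the effect. That is conjecture. The measurement milestones rest on completion, quality, consent and fitness for purpose, and the RCT's primary and secondary objectives are already named.

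The objection does not rescue the sentence itself. If the target difference and the control rate come from elsewhere, the pilot informs the RCT size and does not determine it. The protocol names no outside source for either.

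**Conclusion.** The point holds as a claim that the design cannot meet. The pilot alone cannot determine the power or size of a trial of prebiotic food against standard food, because it observes neither the standard-food rate nor the effect against it. This follows from the described arms and needs no numerical assumption.

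The numerical part is conditional. If the between-arm estimate were used as the RCT effect, its half-width of about 0.74 SD would make the size unreliable. The 21% figures rest further on an assumed true effect of 0.3 SD. For the before/after estimate the problem is bias, which these figures do not measure.

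This should be fixed, but it is not critical. It leaves the pilot's feasibility data, conduct and safety untouched, and harm would arise only if a later trial used the pilot estimates uncritically.

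**What to change.** Change *determine* to *inform* wherever the claim is made: the Sample Size sentence, Objective 3 under Study Objectives, and the heading of item 11. Reword the two sample-size milestones to match. Changing the Sample Size sentence alone would leave the protocol contradicting itself.

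Then add three statements:

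1. The pilot supplies nuisance and feasibility parameters (SD or overdispersion, data completeness, adherence, dropout), and their uncertainty is carried into the RCT calculation. An upper confidence limit for the variance is one way to do this. The 80% limit would multiply the variance by 1.29 with 29 df, but other conventions would serve.
2. The RCT target difference will be a minimum important difference set in advance.
3. The standard-food infection rate will come from external data with a stated range. Neither it nor the target difference will be taken from the pilot's 30-versus-10 or before/after estimates.

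Recruitment, visits and feeding do not change. The cost is that a primary objective is restated and the protocol promises less from the pilot.

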In this study every infant will be sampled and analysed individually before and after intervention, i.e. being assessed as a case/control pair. This “personal” case/control pair-wise analysis will account for differences in infant feeding (e.g. maternal diet, duration of breastfeeding) and can be interpreted as a multiplexed n-of-1 trial (6).

Preparation for Clinical Pilot (Feasibility Study)

To determine the experimental complementary feed for the clinical pilot study we will bioinformatically exploit existing data and knowledge on immune protection-beneficial bacteria that are present in the infant GI microbiome around weaning and known/suggested to be beneficial for the evolving infant GI and systemic immune system. We will then interrogate the (NZ) food space and identify the best whole foods and food components to feed these beneficial bacteria. This systems biology and ecosystem approach differs fundamentally from classical “test feeding” studies

We will select and focus on infant GI bacteria that are known/suggested to (i) promote healthy immunity in exclusively breast-fed infants and remain post-weaning (7); or (ii) colonise the infant GI microbiome around or after weaning and facilitate healthy immune development. The genomes of these selected infant GI microbes should be available and sufficiently annotated. Suggested candidates for (i) are: *Bifidobacterium longum* subspecies *infantis* (*B. infantis*) (8-10) [Guillaume 2009] and *Bifidobacterium animalis lactis* (*B. lactis*) (11-14). Possible candidates for (ii) can be retrieved from completed infant GI microbiome studies that span the breast feeding, weaning and solid food period along the first year of life (7, 15). From the microbiome angle, we will consult the available genomic, bioinformatic and microbiological information to identify whole foods and food components that support the growth of these beneficial infant GI bacteria. This investigation will extend beyond and complement the established research and knowledge on *Bifidobacteria* specifically consuming human milk oligosaccharides (16).

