# **STUDY METHODS/DESIGN**

Ethical Considerations

Ethical approval will be obtained from The Northern B Health and Disability Ethics Committee (HDEC) of the Ministry of Health, New Zealand (HDEC reference number TBC).

Trial Design

Nourish to Flourish is a non-randomised clinical pilot study with an active control involving 40 infants (and mothers) which will examine the feasibility of conducting a randomised controlled clinical trial (RCT) to support immune protection against infection. This study will be conducted in Auckland, New Zealand. The study outline is shown in **Figure 1**.

Participant characteristics

Eligible study participants for the feasibility study are 40 healthy infants 2 to 3 months of age with the expectation that they will be introduced to their first complimentary foods around 6 months of age, and not before 4 months of age, as per the Ministry of Health Food and Nutrition Guidelines (Ref).

Infants will be ineligible for enrolment if they: were born <32 weeks’ gestation; have a developmental disability (i.e., autism, intellectual disability); an illness likely to influence their nutritional status (e.g., a chronic illness known to cause malabsorption, digestive or metabolic disorders); who have a doctor-diagnosed cow’s milk allergy; have health conditions that affect feeding; are undergoing treatment with antibiotics; are receiving a supplement with a pre- and/or probiotic; or whose parents written or spoken English comprehension is likely to make participation difficult for them. The decision to participate and written, informed consent will be obtained by the research team from parents/guardians on the child’s behalf. Infants who were born premature or small for gestational age will also be excluded as they may have special dietary requirements.

Infants will be recruited from urban central and greater areas of Auckland. Recruitment strategies include electronic and print advertising through The University of Auckland, community outreach campaigns including coffee groups, antenatal groups, local newspapers, and appropriate social media platforms.

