**Study Intervention**

Approximately 40 infants aged 2 to 3 months will be recruited for a 6-month study with the intervention starting at around 6 months of age – The NZ Ministry of Health and World Health Organisation recommended age for introducing complementary foods (ref).

The study will be conducted in two stages to enable completion within the tight timeframe. Thirty (30) of the recruited infants will be receive a dietary intervention based on a prebiotic food (candidate food) and 10 infants will receive a probiotic control known to show relevant immune benefit(s) and accepted as an ingredient in infant nutrition. These 10 infants will serve as a positive control to ensure that our study design and methods in principle can detect probiotic-related immune benefit. Envisaged probiotic controls are: *Bifidobacterium longum subspecies infantis (B. infantis)* (ref) and *Bifidobacterium animalis lactis (B. lactis)* (ref).

Researchers will supply the dietary intervention at no cost to the participant. The food will be given to the infants daily in appropriate amounts according to their age and stage of weaning. The amount of food given to the infant will not displace other foods of important nutrient composition in the infant’s diet. The infant will be introduced to the food with their first complementary foods and the food will be consumed daily for the 6-month period of the intervention.

Parents and guardians will be requested to have their infant consume the supplied candidate food or probiotic control each day for a total of 6 months (i.e. from when the child turns 6 months old until they turn 1 year of age). Adherence will be measured using information from a monthly questionnaire with parents or guardians on the average amount of candidate food consumed per day in the previous month.

Outcomes

Parents/guardians will complete daily records of illness through reporting the incidence, severity, and duration of the 9 signs of upper and lower respiratory tract and GI infections. This will be completed throughout the course of the study. Specific consent will be obtained to access medical records for infection-related GP visits, medication prescription and use, and hospitalisation events from 6 to 12 months of age. The infectious nature of the illness will be established by microbiological data, and/or the use of validated questionnaires.

Data Collection

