Faecal samples will be collected at 6, 7.5, 9 and 12 months of age according to a pre-defined protocol. Faecal samples will be used to assess the extent to which the complementary feeding has modulated the infant GI microbiota and to quantify vaccine-specific antibody responses as a non-specific measure of protective antibody responses. Parents/caregivers will be provided with all necessary equipment for the successful collection and storage of stool samples from their infants nappy e.g. gloves, sterile sample container with scoop for the stool sample, zip lock bag, polystyrene box, freezer gel pack, and a rubbish bag. Parents/caregivers will collect samples from the nappy after the participating infant has passed a bowel motion. Scoops present in the sample container will transfer approximately 1 tsp of the stool sample into the sterile tube. Once the lid is secure, the sterile tubes will then be placed in the zip lock bag together with the frozen gel pack and placed in the polystyrene box provided. Samples can be kept at room temperature in the polystyrene box and brought into the pre-arranged clinic appointment within 24 hours.

**Saliva** (baseline, CF1, CF3, and CF6)

Saliva samples will be collected to quantify vaccine-specific antibody responses at 6, 9 and 12 months of age as a non-specific measure of protective antibody responses. Samples will be collected according to a pre-defined protocol. Saliva will be collected using a Salivette. The cotton wool swab is removed from the salivette and placed in the infant’s mouth until saturated (1 to 3 mins). This is achieved through rolling the swab inside the child’s cheek. The swab is replaced in the salivette and capped. Once prepared, samples will be stored at -80°C until analysis.

**Breast Milk** (baseline, CF1, CF3, and CF6)

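### The paired before/after analysis, labelled a multiplexed n-of-1 trial, cannot separate the food from maturation and weaning, so within-infant changes should not be read as food effects or used as such to size the full trial

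*Protocol*

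**What the plan says.** The Statistical methods section describes one design only: "every infant is sampled before and after the intervention, and followed up. Thereby constituting its own case-control pair". The Background, Sample Size and Data Analysis sections add that this analysis "can be interpreted as a multiplexed n-of-1 trial".

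Two claims are made for the pairing. Sample Size and Data Analysis say that the "pairwise analysis will account for differences in infant feeding before the actual intervention". The Background says that it deals with differences in infant feeding, with maternal diet and breastfeeding duration as examples, and sets no limit to the time before the intervention.

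Sample Size and Data Analysis also mention classical case/control analyses alongside the pairwise one, and Data Analysis adds an integrated multi-omics analysis. The groups are "30 infants who will receive the feeding intervention and 10 infants will receive the active control (probiotic) for a period of 6 months", and Trial Design states that there is no randomisation. Study Intervention describes the 10 probiotic infants as a positive control. It also says that the food is introduced with the first solids and continues daily from 6 to 12 months of age.

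**The concern.** An n-of-1 trial gains its strength from switching the same person on and off treatment, usually more than once. Here every infant goes once from off-food to on-food, in the same direction and at about the same age. The switch coincides with the start of weaning, which the Background itself presents as a time of large gut, immune and developmental change. A within-infant difference therefore contains the food, age, other solids, changes in breast milk and formula, and vaccination, with nothing in the pair to divide them.

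This matters even in a feasibility study. Primary objective 4 looks for outcomes that can show a chain of effects from food to immune benefit. Stool samples are to "assess the extent to which the complementary feeding has modulated the infant GI microbiota". The last set of milestones sizes the full trial for infection protection and microbiota change attributed to the food. A before/after mean taken as the food effect would carry maturation into the choice of outcome and into the sample size of the full trial. The positive control is exposed as well: judged before/after, an inert probiotic could seem to confirm that the methods work.

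**Working it through.** **What pairing can and cannot remove.** Write an infant's value before as a + e₁ and after as a + m + f + e₂, where a is whatever is stable in that infant, m is the change that would have occurred anyway and f is the food effect. The difference is m + f + (e₂ − e₁). The stable part a cancels; m does not. The protocol's own text supplies components of m:

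- Study Intervention: food and first solids start together.
- Diet: breast milk is still an important part of the diet in this period, and its volume and formula intake are measured; both can change between the samples.
- Blood and Table 1: first blood is at CF1, given as 4–6 months, and rotavirus and pneumococcal doses are due at 5 months. The CF1 sample may precede or follow those doses, so the CF1-to-CF6 antibody change can depend on that timing.

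**Inputs for the size of the problem.** From Sample Size: 30 infants on the food, 10 on probiotic. That section says "there no sample size calculations are required", so there is no planned effect, SD, alpha or power to reproduce. Assumed here: a paired t-test, two-sided 5%, normally distributed changes, a food effect of zero, and an age drift d in units of the SD of within-infant change.

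**Formula.** P(significant) = P(|T| > t₀.₉₇₅,ₙ₋₁), with T noncentral t on n − 1 degrees of freedom and noncentrality d√n. For n = 30, √30 = 5.477, so the noncentrality is 1.10, 1.64, 2.74 and 4.38 at d = 0.2, 0.3, 0.5 and 0.8.

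| Drift d | n = 30 | n = 24 (assumed 20% loss) | n = 10 |
|---|---|---|---|
| 0 | 5% | 5% | 5% |
| 0.2 | 18.5% | 15.6% | 8.8% |
| 0.3 | 35.5% | 29.1% | 13.6% |
| 0.5 | 75.4% | 65.0% | 29.3% |
| 0.8 | 98.8% | 96.3% | 61.6% |

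In 30 infants, a drift of about 0.53 SD is enough for an 80% chance of a significant result with no food effect. The last column is the chance that an inert probiotic shows a significant before/after change.

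**The group comparison.** With the same drift in both arms and no difference between products, 20,000 simulated trials at each drift from 0.3 to 1.0 SD gave rejection rates of 4.9% to 5.2%. Shared maturation cancels, provided the non-randomised groups mature alike. The detectable difference at 80% power is (1.960 + 0.842) × √(1/10 + 1/30) = 2.802 × 0.365 = 1.02 SD, or 1.05 SD with the t distribution. Adjustment for the CF1 value at an assumed correlation of 0.5 gives 1.05 × √(1 − 0.25) = 0.91 SD. Power is about 27% at 0.5 SD and 57% at 0.8 SD. The quantity estimated is food versus probiotic, so two equally effective products would look alike.

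**The case against.** The best defence is that this is an openly non-randomised feasibility study. Most milestones concern intake, completion, sample collection, recruitment and adverse events. No paired test or significance rule is stated, no section says that a before/after mean will be used as the effect size of the full trial, and the Research Plan gives the full trial a standard-weaning-food arm. All of this is correct. It limits the point to interpretation and planning, but it does not rescue the n-of-1 label or the Background's claim.

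Four stronger readings are tempting, and the protocol does not support them.

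- A reader might infer that the paired analysis is the only one planned. Sample Size and Data Analysis name group and multi-omics analyses too, and their models may be in an analysis plan that is not at hand. No model, however, turns 10 non-randomised infants on an active probiotic into a comparison with ordinary weaning.
- A reader might infer that the Sample Size sentence is false. It covers only feeding before the intervention, and pairing does remove stable, additive differences of that kind. The Background's unrestricted version is the one that fails.
- A reader might infer that nearly any age-related change would be taken for a food effect. At a drift of 0.2 to 0.3 SD the chance is 18.5% to 35.5% in 30 infants; only from about 0.5 SD is it the usual result.
- A reader might infer that infection has no pre-food data, since medical-record access covers "hospitalisation events from 6 to 12 months of age". Outcomes has parents keep daily illness records throughout the study, and Table 1 asks about respiratory infections and GP or hospital visits at baseline and CF1.

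It is also true that stool and urine are sampled at several ages, and that Table 1 includes a baseline at enrolment; only blood is limited to two times. A pre-food interval can show an earlier trend. It cannot show what weaning itself would have done, because weaning and the food begin together.

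**Conclusion.** The point holds in a limited form. The confounding of food with maturation and weaning lies in the design, and an analysis plan could not remove it. The n-of-1 label is unsupported, and the Background's unrestricted claim about feeding is wrong. Neither the paired analysis nor the 30 versus 10 contrast estimates the effect of the food against ordinary weaning.

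The rates of about 19%, 36%, 75% and 99% rest on an assumed paired t-test and assumed drifts; the protocol gives neither. They show how the error grows with the drift and do not predict what will be found. The detectable difference of about 1 SD for the arm contrast rests on all 40 infants contributing and on equal SDs in the two arms. The feasibility endpoints are unaffected.

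**What to change.** 1. Delete the n-of-1 label in the Background, Sample Size, Statistical methods and Data Analysis sections. Limit the claim about feeding to stable differences that exist before the intervention.
2. Report within-infant changes with 95% confidence intervals as descriptive trajectories, and state that they are not food effects.
3. Present the arm contrast as an exploratory food-versus-probiotic comparison, adjusted for the CF1 value, age at sampling and feeding at CF1. State its detectable difference of about 1 SD and its non-randomised basis. For blood markers it is available at CF6 only, because Table 1 has no blood at CF3.
4. Carry variances, within-infant correlations, event rates and completion rates into the sizing of the full trial, but not the before/after mean change as the food effect.

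The cost is wording. The downside is a less favourable statement of what the pilot can show. Medical-record consent need not be extended, because parent-reported illness already covers the pre-food period.
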